### Statistical analysis

The frequency distributions of primary and secondary study endpoints will be compared across the groups using 2 × 2 contingency tables. Continuous data will be presented as mean values ± standard deviation or medians with their respective interquartile range. Categorical variables will be presented as absolute numbers with percentages. Measures of association of categorical data will be derived from Fisher’s exact test. Analysis of continuous data will rely on the Mann-Whitney *U* test or Student’s *t* test. Comparisons of functional connectivity between regions of interest on pre- and postoperative rs-fMRI will be performed with the Wilcoxon matched-pairs test. Correlations between multiple variables of interest will be examined using Spearman’s or Pearson’s correlation coefficients. The choice between parametric and nonparametric statistical tools will be based on the normality of distribution. A two-tailed *P* value of less than 0.05 will be considered significant for all deployed statistical calculations. The data will be processed using the IBM SPSS Statistics software package (version 20.0; Somers, NY, USA).

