### Sample size

The estimation of the approximate sample size for this study was based on an exact sign (binomial) test, assuming an effect size of 0.20. To account for potential postoperative contraindications for MRI and study consent withdrawals, an estimated 70 patients will be required to test the null hypothesis with an α value of 0.05 and a power of 0.90 [18].

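### Fisher's exact test for the binary primary composite is valid but conservative; Boschloo's exact test holds the same 5% level, never has less power, and is a cheap improvement

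*Protocol article*

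**What the plan says.** All references are to the Methods of the protocol article.

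- **Statistical analysis.** Primary and secondary endpoint frequencies are tabulated 2 × 2 by arm. On the test, the section says "Measures of association of categorical data will be derived from" Fisher's exact test. On the threshold it says "A two-tailed *P* value of less than 0.05 will be considered significant", and applies this to every calculation. SPSS version 20.0 is the named software.
- **Sample size.** The calculation is "based on an exact sign (binomial) test", "assuming an effect size of 0.20". It concludes that "an estimated 70 patients will be required to test the null hypothesis with an α value of 0.05 and a power of 0.90". The total already allows for MRI contraindications and withdrawals, but no loss rate is given.
- **Not stated.** The article gives no event rate for either arm and no allocation ratio.

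The test is therefore a choice that the article makes, not a detail left to an unseen analysis plan.

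**The concern.** Randomization fixes the arm sizes but not the total number of patients with an event. Fisher's test conditions on that total. In small samples the conditional distribution is coarse, so the test usually cannot reach its nominal level and rejects less often than 5% under the null hypothesis.

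Boschloo's test uses Fisher's p value as its ordering statistic and calibrates the cut-off over all possible event rates. Its rejection region contains Fisher's, so it cannot have lower power at any pair of rates, and its type I error still stays at or below 5%.

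What is at stake is that a result meeting the trial's own 5% standard may be reported as non-significant only because of the test chosen. At 35 per arm, 24/35 v 15/35 gives Fisher P = 0.053 and Boschloo P = 0.034. Neighbouring results behave the same way: 19 v 10, 20 v 11, 21 v 12, 22 v 13, 23 v 14 and 25 v 16 all have a Fisher P between 0.051 and 0.055, and Boschloo's test rejects at each.

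**Working it through.** **Inputs.** From the article: total of 70, two-sided 0.05, power 0.90, effect size 0.20, Fisher's exact test on a 2 × 2 table. Assumed: 1:1 allocation, a binary composite (implied by the 2 × 2 table), and all event rates. The 0.20 is read as a risk difference for the two-arm calculations.

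**Step 1: the plan's own figure.** Take a two-sided exact sign test of 0.50 against 0.70. Power first reaches 0.90 at n = 65 (reject at 41 or more of 65 or the mirror image; actual alpha 0.046, power 0.910). With an assumed loss of 7%, 65 / (1 − 0.07) = 69.9, which rounds to 70. So 70 can be read as about 65 evaluable patients plus an allowance for loss. This is an inference, because the loss rate is not given.

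**Step 2: true size.** For arms n1 and n2 and rejection region R, with b the binomial probability:

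size(π) = Σ over (x, y) in R of b(x; n1, π) · b(y; n2, π), maximised over π.

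For Fisher's test, R is every table with two-sided P < 0.05. For Boschloo's test, R is every table with Fisher P at or below the largest cut-off that keeps the maximum size at or below 0.05. At 35 v 35 that cut-off is 0.078.

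Results at 35 v 35:
- Fisher: maximum size 0.0294, at a common rate of about 0.35; 0.024 at a rate of 0.50.
- Boschloo: maximum size 0.0480.

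**Step 3: power at 35 v 35.** Power = Σ over R of b(x; n1, p1) · b(y; n2, p2).

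| Assumed rates | Fisher | Boschloo | Gain (points) |
|---|---|---|---|
| 0.30 v 0.10 | 0.455 | 0.542 | 8.7 |
| 0.40 v 0.20 | 0.357 | 0.445 | 8.8 |
| 0.50 v 0.30 | 0.312 | 0.379 | 6.7 |
| 0.60 v 0.40 | 0.280 | 0.361 | 8.1 |

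The pairs 0.70 v 0.50, 0.80 v 0.60 and 0.90 v 0.70 mirror the first three rows. At a difference of 0.30, the gain is 6.5 points for 0.50 v 0.20 and 7.8 for 0.60 v 0.30. It shrinks further at larger differences: 2.0 to 6.3 points at 0.35 and 0.1 to 4.0 at 0.40.

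**Step 4: other evaluable splits.** The same enumeration was run over the seven pairs at a 0.20 difference (higher rate 0.30 to 0.90).

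| Evaluable split | Fisher maximum size | Gain (points) |
|---|---|---|
| 35 v 35 | 2.9% | 6.7 to 8.8 |
| 36 v 34 | 3.8% | 2.0 to 6.3 |
| 37 v 33 | 3.9% | 0.4 to 6.3 |
| 35 v 34 | 3.9% | 2.0 to 6.6 |
| 33 v 33 | 3.6% | 1.2 to 9.4 |
| 33 v 32 | 4.6% | 0.0 to 5.8 |
| 34 v 31 | 4.6% | 0.1 to 5.8 |
| 30 v 30 | 2.7% | 4.9 to 8.1 |

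At 33 v 32, which is 65 evaluable patients, the gain is nil for 0.60 v 0.40 and for 0.70 v 0.35, and 0.1 point for 0.70 v 0.40.

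**The case against.** The strongest reply is that nothing in the article is wrong. Fisher's test is standard for small 2 × 2 tables, and a true size below 5% does not breach a 5% limit. Preference between conditional and unconditional tests is a long-running debate. This stands as far as validity goes: the point is lost efficiency, not an error or a contradiction. It does not dispose of the point. Boschloo's test gives the same guarantee at the article's own threshold and cannot lose power, so the usual reason for preferring Fisher's test does not separate the two.

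The second reply is that the largest figures need exactly 35 v 35 analysed. The total of 70 already includes an allowance for loss, Table 1 lists postoperative exclusions, and the day-7 MRI feeds the primary composite. Fewer than 70 evaluable patients and slightly unequal arms are therefore to be expected. This stands. A reader might infer from the 35 v 35 case that the true error is generally about half of 5%, or that 6 to 9 points of power are always lost. Step 4 does not support either inference: one lost patient moves the maximum size from 2.9% to 3.9%, and at 33 v 32 it is 4.6%.

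The third reply is that the change does not rescue the trial. This also stands. The article sizes a two-group comparison with a sign test, and that mismatch matters far more than the choice between two exact tests.

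**Conclusion.** This is a cheap improvement, not a correction of an error. Assuming 1:1 allocation, Fisher's maximum true size is about 2.9% at 35 v 35 and about 2.7% to 4.6% over the nearby evaluable splits examined. At an assumed risk difference of 0.20, Boschloo's test gains about 7 to 9 points of power at 35 v 35 and about 0 to 9 points across those splits. That it is never less powerful holds whatever the split and event rates. The size of the gain depends on both, and the article gives no event rates.

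A reader might also infer that switching tests would restore "a power of 0.90". It would not. At 35 per arm and a 0.20 difference, power runs from about 0.28 to 0.46 with Fisher's test and from about 0.36 to 0.54 with Boschloo's. The usual two-proportion formula asks for about 109 per arm (0.40 v 0.20) to 130 per arm (0.60 v 0.40) for 90% power.

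**What to change.** Before unblinding, replace Fisher's test for the primary composite with one sentence such as: *The primary composite will be compared between arms with Boschloo's unconditional exact test at a two-sided 5% level, with tables ordered by the two-sided Fisher p value.* The ordering should be named because two-sided versions of the test can differ, especially when the arms are unequal.

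The cost is one sentence and a test that readers know less well and that is run outside SPSS 20, in free software. No extra patients or data are needed. Using the same test for the other binary endpoints, or adding a score-based 95% confidence interval for the risk difference, is optional. The sample-size basis needs separate attention.

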**Methods:**

Patients scheduled for elective coronary artery bypass grafting with the use of cardiopulmonary bypass will be screened for the study. Eligible patients will be randomized to undergo either a validated RIPC protocol or a sham procedure. The RIPC will be induced by inflation of a blood pressure cuff to 200 mmHg for 5 minutes, followed by a 5-minute reperfusion period. Three sequences of interchanging cuff inflations and deflations will be employed. Neurocognitive testing and MRI imaging will be performed preoperatively and on postoperative day 7. Paired pre- and postoperative neurocognitive and neuroimaging data will then be compared. The primary composite outcome measure will consist of new ischemic lesions on brain MRI, postprocedural impairment in brain connectivity on resting-state functional MRI (rs-fMRI), and significant new declines in neurocognitive performance. The secondary endpoint measures will be the individual components of the primary endpoint measures, expressed as continuous variables, troponin T release on postoperative day 1 and the incidence of major adverse cardiovascular events at 3 months postoperatively. Major adverse cardiovascular events, including accumulating cardiovascular mortality, stroke, nonfatal myocardial infarction, and rehospitalization for ischemia, will form a composite endpoint measure.

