### Outcome definitions

The primary composite outcome will consist of new ischemic lesions on brain MRI, impairment in brain connectivity on resting-state functional MRI (rs-fMRI) and postoperative cognitive dysfunction. Postoperative cognitive dysfunction will be defined as a decrease of at least one standard deviation in at least two components of neurocognitive testing.

The secondary endpoint measures will be:Volumetric quantification of areas of new ischemic lesions on structural brain MRI.Changes between pre- and post-rs-fMRI, expressed as continuous variables and compared among the intervention and control arms.Percentage declines in individual neurocognitive tests.Troponin T release on postoperative day 1.Incidence of major adverse cardiovascular events at 3 months postoperatively.

Major adverse cardiovascular events will comprise a composite endpoint measure, consisting of cardiovascular mortality, stroke, nonfatal myocardial infarction, and rehospitalization for ischemia. Perioperative myocardial infarction will be adjudicated in accordance to the definition supplied by the Joint European Society of Cardiology/American College of Cardiology Foundation/American Heart Association/World Heart Federation Task Force for the Redefinition of Myocardial Infarction [31]. Briefly, a troponin T value ten times the 99th percentile of the upper reference limit, coupled with electrocardiogram changes, new-onset coronary artery (or graft) occlusion, or imaging evidence of new wall motion abnormalities will meet the criteria for perioperative myocardial infarction [31]. Stroke will be a defined on the basis of either a new focal deficit lasting >24 hours or an imaging study suggestive of a new lesion in patients with prompt neurological recovery [32].

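### The only test named for resting-state fMRI is a within-patient pre/post test, while the secondary endpoint is a between-arm comparison of change; the plan does not link the two

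*Protocol article*

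**What the plan says.** In the protocol article, the Outcome definitions section lists as a secondary endpoint "Changes between pre- and post-rs-fMRI, expressed as continuous variables and compared among the intervention and control arms". This is a randomized comparison of a continuous change.

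The Statistical analysis section has three sentences that bear on how it would be tested:

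- A frequency rule: "The frequency distributions of primary and secondary study endpoints will be compared across the groups using 2 × 2 contingency tables".
- A general rule for continuous data: "Analysis of continuous data will rely on the Mann-Whitney" test, with Student's t test as the alternative. Both are taken here as two-sample tests.
- A sentence for rs-fMRI alone, directly after the general rule: "Comparisons of functional connectivity between regions of interest on pre- and postoperative rs-fMRI will be performed with the Wilcoxon matched-pairs test".

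The same section applies a two-tailed 0.05 threshold to every calculation. It does not say whether the Wilcoxon test is pooled over patients or run by arm, or what conclusion it is meant to support.

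Two other places describe the imaging comparison as before versus after surgery, without mentioning arms: the Methods part of the abstract ("Paired pre- and postoperative neurocognitive and neuroimaging data will then be compared") and the rs-fMRI row of Table 2.

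**The concern.** The trial asks a between-arm question: "Eligible patients will be randomized to undergo either a validated RIPC protocol or a sham procedure". A matched-pairs test compares each patient with himself or herself. Pooled over all patients, it asks whether connectivity differs before and after surgery. Run separately by arm, it asks that question twice. Neither version estimates or tests the difference between RIPC and sham.

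A specific sentence placed straight after a general one can be read as the exception to it. An analyst who reads it so would run the Wilcoxon tests and could stop there. The report might then show a significant fall in one arm and none in the other, and a reader could take that as evidence of protection although no between-arm test had been done. At stake is the credibility of any connectivity claim for RIPC made from this secondary endpoint.

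**Working it through.** The plan gives no figure for this point, so there is none to reproduce. The check sets the text side by side and then sizes the risk and the remedy.

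**1. Does each stated rule provide the comparison that the endpoint asks for?**

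| Rule in Statistical analysis | Compares arms? | Fits a continuous rs-fMRI change? | Linked to rs-fMRI by name? |
|---|---|---|---|
| 2 × 2 tables across groups | Yes | No, needs a yes/no outcome | No |
| Mann-Whitney or t test | Yes | Yes | No |
| Wilcoxon matched-pairs, pre vs post | No | Within patient only | Yes |

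The rule that fits is not named for the endpoint, and the rule that is named does not fit.

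**2. What happens if one-arm-only significance is read as a treatment effect?** Assume no true arm difference and within-arm power *p* in each arm. The chance that exactly one arm is significant is 2*p*(1 − *p*), and half of those cases favour RIPC.

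- *p* = 0.50: 2 × 0.50 × 0.50 = 50%, with 25% favouring RIPC. This is the maximum of the formula.
- *p* = 0.80: 2 × 0.80 × 0.20 = 32%, with 16% favouring RIPC.
- *p* = 0.95: 2 × 0.95 × 0.05 = 9.5%, with 4.75% favouring RIPC.

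**3. Simulation of the same situation.** Inputs: 35 patients per arm (assumed: the planned 70 split equally with no losses), normally distributed changes with SD 1, the same true change in both arms, 3,000 runs, two-sided 0.05.

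| Common change (SD) | Wilcoxon significant in one arm only | Pooled Wilcoxon significant | Mann-Whitney on change, between arms |
|---|---|---|---|
| 0 | 8.6% | 4.3% | 4.7% |
| 0.3 | 46.9% | 68.8% | 5.3% |
| 0.4 | 47.3% | 88.6% | 4.7% |
| 0.5 | 30.8% | 98.0% | 4.3% |
| 0.8 | 1.2% | 100% | 5.4% |

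The between-arm test stays near 5% throughout. The pooled Wilcoxon test responds to the common change alone. The one-arm-only pattern ranges from 1.2% to 47.3%, depending on how large the common change is.

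**4. What does a between-arm analysis gain from adjusting for the preoperative value?** Let the pre and post values have equal variance σ² and correlation *r*.

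- Variance of the change score: 2σ²(1 − *r*).
- Residual variance under ANCOVA: σ²(1 − *r*²).
- Ratio: (1 − *r*²) / [2(1 − *r*)] = (1 + *r*)/2.
- *r* = 0.3: 1.3/2 = 0.65. *r* = 0.7: 1.7/2 = 0.85.

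The documents give no *r*; 0.3 to 0.7 is an assumed range.

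**5. Detectable difference.** With 35 per arm, two-sided 0.05 and 90% power, a t test on change detects (1.960 + 1.282) × √(2/35) ≈ 0.77 SD of the change (0.79 for Mann-Whitney). ANCOVA multiplies the t-test figure by √[(1 + *r*)/2]. This gives 0.775 × √0.65 ≈ 0.62 at *r* = 0.3 and 0.775 × √0.85 ≈ 0.71 at *r* = 0.7, in the same units.

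**The case against.** The strongest reply is that the arm comparison is already planned. The endpoint is defined as "expressed as continuous variables and compared among the intervention and control arms", and the sentence just before the Wilcoxon one gives two-sample tests for continuous data. Read together, they yield a Mann-Whitney or t test on rs-fMRI change by arm. A within-patient test can sit beside that, since Table 2 treats the before/after pattern as an rs-fMRI target in its own right. Much of this stands, and it rules out three stronger readings that a reader might infer.

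- *That the plan discards the randomized comparison or contradicts itself.* It does not. The comparison is stated as the endpoint, a suitable general test is stated, and both analyses can be run. What is missing is the link between them and the role of the Wilcoxon test.
- *That the primary result is exposed.* The composite does include "impairment in brain connectivity on resting-state functional MRI (rs-fMRI) and postoperative cognitive dysfunction", but its frequency is compared across groups by 2 × 2 table. A group-level Wilcoxon test gives no patient an impairment status, so it does not decide the composite.
- *That 50% or 32% is the plan's error rate.* No section tells the analyst to test by arm and infer protection from significance in one arm only. The figures illustrate that misreading and vary widely with the assumed power.

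One might also say that matching tests to endpoints belongs in an analysis plan that is not shown. That would excuse silence. Here the article does name a test for this endpoint's data, and that test cannot make the comparison in the endpoint's definition. The choice of ANCOVA over a two-sample test on change is an improvement in efficiency; not having chosen it is no error.

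**Conclusion.** The point holds in a narrow form, at moderate to minor severity. The one test tied by name to rs-fMRI cannot compare RIPC with sham, the general rule that could is not linked to the endpoint, and the purpose of the pre/post test is not stated. The consequence is limited to the secondary rs-fMRI endpoint.

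The conclusion about the text needs no assumption. The sizes do. The illustrative false-signal figures assume no true arm difference and a reader who draws the one-arm-only inference. The detectable differences assume 35 analysable patients per arm. The variance ratio of 0.65 to 0.85 assumes equal pre and post variances, a linear relation and a correlation of 0.3 to 0.7.

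**What to change.** Amend the Statistical analysis section so that it says the following:

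- Inference about RIPC on rs-fMRI is the between-arm comparison of postoperative connectivity by ANCOVA, with the preoperative value as covariate, reported as an arm difference with 95% CI.
- If the ANCOVA assumptions fail, the comparison is a Mann-Whitney test on per-patient change.
- The pre/post Wilcoxon matched-pairs tests are descriptive and support no conclusion about RIPC.

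This brings the section into line with the Outcome definitions. The cost is a few sentences. Both scans are already scheduled for every patient, so no new data are needed. The article reports recruitment as ongoing, so the wording can be settled before analysis.

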## Discussion

Alternating cycles of nonlethal ischemia and reperfusion induce an endogenous response that renders tissues more tolerant to a subsequent prolonged ischemic ictus [3]. In contrast with ischemic preconditioning, which is essentially restricted to the experimental arena, RIPC has the capacity for translation into the clinical domain [9]; it induces ischemic tolerance in distant organs by provoking ischemia in tissues that are both easily accessible and resistant to noxious stimuli. In this prospective randomized trial, RIPC will be evaluated as a neuroprotective strategy in the cardiac surgical arena. We believe that the high frequency of discrete neurological dysfunction following cardiac surgery, coupled with the proven benefit of RIPC on the induction of ischemic tolerance in other organs, constitutes a sound basis for this research. A strategy that would increase ischemic tolerance within the ischemic penumbra could potentially yield superior neurological outcomes.

In this prospective randomized study, a homogenous cardiac surgical patient population will be subjected to a validated RIPC protocol. Previous research has focused on the reduction of myocardial ischemic injury after cardiac surgery induced by RIPC [1]. To the best of our knowledge, this is the first trial that will specifically address the neuroprotective value of this strategy in patients undergoing surgical myocardial revascularization. The comprehensive battery of brain MRI tools that will be used, coupled with neurocognitive testing, will allow for the identification of discrete neurologic injuries, thereby increasing the trial’s diagnostic sensitivity.

The etiology of brain injury following cardiac surgery is multifaceted, and not all of its potential triggers can be addressed in a single trial. Our study will focus on a strategy hypothesized to reduce the impact of ischemia on end-organ performance.

While the trial will enroll patients from the lower-risk stratum of the contemporary cardiac surgical practice, the fact that the pathophysiology of brain ischemia is no different in higher-risk patients will allow for the results of this trial to be generalized onto a wider surgical cohort. Should the preoperative implementation of a RIPC protocol result in improvement in postoperative neurologic outcomes, the RIPCAGE trial could meaningfully impact on the standard of care in cardiac surgical patients.

## Trial status

Patient recruitment for the study is currently ongoing.

## Abbreviations

MRI: magnetic resonance imaging
RIPC: remote ischemic preconditioning
RIPCAGE: Impact of Remote Ischemic Preconditioning preceding Coronary Artery Bypass Grafting on Inducing Neuroprotection Trial
rs-fMRI: resting-state functional magnetic resonance imaging.
